### Recruitment Strategy and Retention

Patients will be recruited by convenient sampling as they report for medical services at the HIV/TB clinic of MRRH. The recruitment of the participants will follow the existing diagnosis and point-of-care procedures at both study sites. The clinic receives an average of 10 new cases per day. Considering both our inclusion and exclusion criteria, we hope to recruit an average of 4 patients per day, resulting in an average total of 88 patients per month. This recruitment plan is achievable based on the rate of patients’ inflow at the clinic. Additionally, sputum sample collection is not an invasive method that would scare away patients, so we do not anticipate any major challenges with patient retention. However, we will factor in a possible 10% dropout rate among patients, and thus, the final sample size will be increased by 37 more patients, resulting in a total of 406 patients, as previously mentioned.

### Recruitment Site Selection

We have selected Uganda for this study because the country ranks high among the severely affected nations with HIV and TB pandemics. This is particularly true in western Uganda, where Mbarara (the proposed study site) is located. This subpopulation is also ranked among those most at risk of opportunistic fungal coinfections, yet it has been grossly ignored. Opportunistic pulmonary fungal coinfections are not uncommon among the immunosuppressed cohort, such as patients with HIV. We have selected patients suspected of having TB because most of the opportunistic pulmonary fungal infections present like TB, and therefore, are often missed during routine diagnosis. We have selected Mbarara Hospital as the study site because it is a regional referral hospital for the western region of Mbarara and a treatment center for patients with HIV or TB. Thus, we will have easy access to our study cases due to the high incidence of HIV or TB in this community. However, several population-based studies have been conducted in the past, focusing on HIV and TB, but are not associated with fungal coinfections [33,34]. Additionally, Mbarara University of Science and Technology has the infrastructure to handle most of the study demands. For instance, the Department of Microbiology in the Faculty of Medicine hosts a microbiology laboratory with medical mycology and TB units that have the capacity to respectively perform routine fungal or TB-based sputum analytical protocols, such as TB and GeneXpert testing, potassium hydroxide, and lactophenol cotton blue staining, as well as fungal and bacterial cultures. Additionally, the department has the capacity to do molecular-based procedures, including DNA isolation, polymerase chain reaction (PCR) amplification, and sequencing. The Department of Microbiology has also established collaborations with both national and international institutions, such as the Infectious Diseases Institute of Makerere University, Gulu University, Soroti University, and Muni University in Uganda; Massachusetts General Hospital and University of Minnesota in the United States; University of Birmingham, Sheffield University, and University of Exeter in the United Kingdom; and University of Aberdeen in Scotland.

### Approach and Methodology

#### Aim 1: Determining the Burden and Etiological Profiles of Fungal Coinfections Among Patients Suspected of TB

Patients' sputum samples will be collected and cultured on both fungal and bacterial media for either organism’s isolation. The isolates will be identified and profiled accordingly using conventional phenotypic and genomic-based assays. Total DNA will be extracted from the same sputum samples using a bead-beating phenol-chloroform approach. PCR primers targeting region 2 intergenic transcribed spacer (ITS2) will be used to amplify the fungal DNA present in the sputum samples; the amplified DNA will then be sequenced by Illumina MiSeq technology. This approach has been demonstrated to sensitively identify and determine the relative abundance of all fungi present in similar respiratory samples [35]. In this study, we will use this approach to identify the most abundant fungi present and detect any potential coinfections, which maybe challenging to identify using traditional culture methods. Fungal data will be analyzed using Mothur and the R statistical package Phyloseq (R Core Team) and will be speciated with reference to the UNITE2 database. Fungal quantitative PCR will be applied to determine the total burden of fungi present in each sample. Shotgun metagenomics will also be applied to a subset of samples. This metagenomics approach will reveal genomic detail of the fungi present, which will potentially include antimicrobial resistance genes and virulence genes and provide further typing information that reveals common clones or transmission among patients. Using long-read technology, the Oxford Nano pore GridION has the advantage of being a rapid sequencing technology that has shown promise as a rapid point-of-care test for the identification of microorganisms in clinical samples. As such, the use of this technology in this study may also reduce the time until diagnosis for fungal infections.

#### Aim 2: Establishing and Characterizing Microbial Communities Associated With Patients Suspected of Having TB

16S ribosomal RNA (rRNA) gene sequencing will be used to target the bacterial communities present in the same samples, using the same DNA extract, to identify bacterial coinfections. The results obtained will be used to describe the bacterial communities present in the sputum samples and then will be integrated with ITS2 fungal data [13,36-38]. To determine the association with the host phenotypes, the clinical metadata, including but not limited to age, gender, BMI, race or tribe, behaviors, and immune status, will be used to determine the association between fungal and bacterial communities with host phenotypes. For correlations between taxa, a combination of 16S rRNA gene and ITS2 sequencing data from the same samples will be used. Co-abundance patterns of bacteria and fungi will reveal potential interactions between and within fungal-bacterial communities, which can be further explored using DNA-independent methods in Aim 3. Both fungal-fungal, bacterial-bacterial and fungal-bacterial relationships will be interrogated using appropriate software packages, such as SparCC [38,39].

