### Selection Criteria

The target population under study consists of patients suspected of TB at MRRH. Participants will be included if they are 18 years and older, provide consent, and have at least one of the following qualities: presenting with PTB-like symptoms, having no prior history of TB, testing positive or negative on smear test and GeneXpert test, exhibiting lipoarabinomannan antigen positivity along with persistent respiratory symptoms, and being on anti-TB treatment and severely ill yet able to produce sputum. Conversely, HIV-positive or HIV-negative patients who have TB-like symptoms but are on anti-TB treatment with a favorable prognosis will also be included. Patients who are on anti-TB treatment and severely ill but unable to produce sputum, critically ill patients, and pregnant women will be excluded from the study. Patients who are critically ill are excluded because their condition may cause delays in sample collection and obtaining consent, which would impact the recruitment process. Additionally, pregnant women suspected of TB are excluded since they are managed differently according to TB guidelines.

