## Results

Study design, ethical review, approval, and research registration have all been completed. Patient enrollment commenced in March 2022. Most of the enrolled patients have completed their 2 visits. Patient enrollment was completed in June 2023, and the study results will be submitted for publication in late 2023.

We will share the study findings with the department of Microbiology, Faculty of Medicine, Mbarara University of Science and Technology; Ministry of Health Uganda; and other partner nongovernment organizations working with TB and related coinfections. We will discuss the scope, impact, and limitations of pulmonary fungal coinfections and bacterial fungal synergism based on our study findings. We hope to achieve technical and policy-level interventions, conduct capacity building, and increase public awareness of microbial ecological evolution. Finally, we will write abstracts and manuscripts for international conferences to an international audience and for peer-reviewed journals, respectively.

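### As described, the fungal-bacterial co-abundance analysis does not use the host variables the study records, so a shared host driver such as immune status can appear as a potential interaction

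*Protocol article*

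**What the plan says.** The Aim 2 section of the protocol article sets out two analyses, one after the other.

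- **Host phenotypes.** The variables listed are "the clinical metadata, including but not limited to age, gender, BMI, race or tribe, behaviors, and immune status", and they "will be used to determine the association between fungal and bacterial communities with host phenotypes".
- **Taxon-to-taxon correlations.** The input is given separately: "For correlations between taxa, a combination of 16S rRNA gene and ITS2 sequencing data from the same samples will be used". Fungal-fungal, bacterial-bacterial and fungal-bacterial relationships "will be interrogated using appropriate software packages, such as SparCC". No host variable is mentioned for this step.

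The section then says how the result will be read: "Co-abundance patterns of bacteria and fungi will reveal potential interactions between and within fungal-bacterial communities, which can be further explored using DNA-independent methods". The follow-up belongs to Aim 3, where the authors hope to infer ecological relationships such as mutualism and competition.

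The sample is mixed. Under Selection Criteria, "HIV-positive or HIV-negative patients who have TB-like symptoms but are on anti-TB treatment with a favorable prognosis will also be included", alongside other patients with TB-like symptoms. Under Recruitment Site Selection the article itself links immune status to fungi: "Opportunistic pulmonary fungal coinfections are not uncommon among the immunosuppressed cohort, such as patients with HIV".

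**The concern.** Two taxa can be unrelated within every kind of patient and still be correlated across a mixture of patient types, if the patient type shifts both. Shifts in the same direction give a positive correlation, which invites a reading of synergism. Shifts in opposite directions give a negative one, which invites a reading of competition or antagonism. A marginal correlation cannot tell either from a real interaction, and measuring absolute instead of relative abundance would not help.

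A shared driver is plausible on the article's own account. It ties fungal coinfection to immunosuppression. Under Previous Findings it describes pulmonary TB as especially common with HIV, which supplies one bacterial example. Immune status is already recorded, but the text uses it in the neighbouring analysis and not in this one. What is at stake is which pairs go forward to Aim 3 as candidate interactions and how the Aim 2 network is described.

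**Working it through.** **The plan's own figure.** Z²P(1−P)/d² = 1.96² × 0.4 × 0.6 / 0.05² = 368.8, so 369. With the finite-population correction for 195,013 it is 368.1, again 369. Then 369 × 1.10 = 405.9, so 406. Both stated figures reproduce and neither is disputed. I use n = 369, with one value per patient and taxon.

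**Assumptions, because the article gives none of these.** A binary host driver (say HIV) has prevalence p. It shifts the log abundance of the fungus by a and of the bacterium by b, in within-group SD units. Within each group the two taxa are independent, so there is no interaction. A two-sided test at 0.05 is used. The Abstract states P<.05 alongside odds ratios, so applying it to correlations is illustrative.

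**Induced correlation.**

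r = p(1−p)ab / √[(1 + p(1−p)a²)(1 + p(1−p)b²)]

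For a = b = d this becomes p(1−p)d² / (1 + p(1−p)d²).

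**Chance of P<.05.** With z = atanh(r) × √(369 − 3) = atanh(r) × 19.13, the probability is Φ(z − 1.96) + Φ(−z − 1.96).

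Worked case, p = 0.5 and d = 0.5: r = 0.0625/1.0625 = 0.059; z = 1.13; probability 20%.

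| Shifts (SD) | r, p = 0.5 | Chance of P<.05, p = 0.5 | Chance of P<.05, p = 0.3 |
|---|---|---|---|
| 0.3 and 0.3 | 0.022 | 7% | 6.5% |
| 0.5 and 0.5 | 0.059 | 20% | 16% |
| 0.75 and 0.75 | 0.123 | 66% | 53% |
| 1 and 1 | 0.200 | 97% | 92% |

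Unequal shifts, p = 0.5, a = 1, b = 0.2: r = 0.05/√(1.25 × 1.01) = 0.0445; z = 0.85; probability about 14%.

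**Check on compositional data.** A simulation used separate fungal and bacterial compositions: 50 taxa each, 5 affected in each, 10,000 reads, centred log-ratio correlations, n = 369 and 200 replicates. Without adjustment, affected pairs reached P<.05 in 12% (p = 0.3) to 15% (p = 0.5) of cases at 0.5 SD, and in 80% to 91% at 1 SD. After the driver was regressed out, the rate was 4.7% to 5.6% throughout.

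**Does another section repair it?**

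- The Abstract's multivariate schemes concern factors associated with the etiological profile.
- Aim 3 mentions differing patient conditions only for the genome-scale model, which is to be attempted, and names no host covariate.
- Expected Deliverables promises integration with clinical information in general, without tying it to co-abundance.
- Strengths and Limitations concedes a lack of capacity for metabolomics experiments, so the Aim 3 follow-up is not a secure safeguard.

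**The case against.** The strongest reply is that this is a condensed article reporting an exploratory step. It neither rules out covariates nor fixes the software, and it speaks only of potential interactions with follow-up. Covariate handling could sit in a fuller plan.

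Much of that stands, and it rules out several stronger readings:

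- A reader might infer that the correlations rest on sequence data alone by decision. The text names sequence data and no covariate; it does not exclude one.
- A reader might infer that a confounded pair will be reported as an interaction. The article's wording is more cautious and leaves room for follow-up.
- A reader might argue that the named package cannot take covariates. The article does not describe the package and offers it only as an example, and nothing stated prevents running it within strata.
- A reader might treat co-abundance as the study's central result. The Abstract's primary outcome is the overall fungal and bacterial diagnostic profile.
- A reader might quote only the 97%. That needs a shift of 1 SD in both taxa. At 0.3 SD the rate is close to nominal, and unequal shifts reduce it sharply. Apart from TB, the article gives no evidence that immune status shifts bacterial taxa.

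The reply does not dispose of the point. The section states the input to the correlations, gives the host variables a separate use, and states the interpretation. Followed as written, it draws an inference that the described analysis cannot support. That is more than a detail left for later.

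**Conclusion.** The concern holds in a limited form. As Aim 2 is described, the co-abundance analysis does not use the recorded host variables, and its patterns are read as potential interactions in a sample of mixed HIV status and anti-TB treatment. A shared host driver can therefore appear as a potential interaction.

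The inflation ranges from trivial to near-certain, depending on driver prevalence and on how far each taxon shifts. The article gives neither, so the percentages illustrate the risk and do not predict it. No stated figure changes, and the primary outcome is untouched. The change should be made because it is cheap and conditions mainly on variables already held, and because it decides which pairs are taken forward.

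**What to change.** Amend the correlation step in Aim 2 as follows.

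1. Estimate fungal-bacterial correlations within strata of immune/HIV status and anti-TB treatment, pooled on the Fisher z scale. Alternatively, correlate log-ratio residuals after regression on those two variables plus age; this suits the case where a stratum is very small.
2. Carry a pair forward to Aim 3 as a candidate interaction only if it persists after conditioning and keeps its sign.
3. Show the unadjusted network alongside, and call its patterns co-occurrence.
4. Keep BMI for a sensitivity analysis. In a cross-sectional study it may be a consequence of infection, and conditioning on it could itself bias the correlation.

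Anti-TB treatment is not named in the metadata list, but the list is open and treatment status is needed for eligibility; confirm that it is held in the data set.

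**Cost.** The Results section says "Patient enrollment was completed in June 2023", so this is a change of analysis wording and a little computation, with no new sampling. Pooling over four strata leaves 369 − 4 × 3 = 357 in place of 366, a loss of 9, and √(366/357) = 1.013, so standard errors rise by about 1.3%. Some pairs may drop out. Conditioning removes only measured drivers, so a surviving pair remains a candidate and not a demonstrated interaction.

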### Statistical Analysis Plans and Power Calculations (Sample Size)

Based on the preliminary study, the prevalence of fungal coinfections among patients suspected of TB has been previously determined to be 40% using Kish-Leslie formula (n=Z^2^ P (1-P)/ d^2^) for determining the sample size in a cross-sectional study. In this formula, n is the sample size, Z (1.96) is the statistic for the level of confidence, P (0.4) is the estimated prevalence, and d (0.05) is the margin of error for the confidence interval. Using the Open Epi calculator, considering a population of 195,013 for Greater Mbarara, the sample size was determined to be 369 patients. Since we anticipate a 10% dropout rate, we will recruit 406 patients. From these patients, only 2 sputum samples will be collected—an on-spot sample on the day of recruitment and an early morning sample the following day, making a total of 812 samples to be collected. Obtained data will be analyzed using appropriate software, such as GraphPad (GraphPad Software Inc), Stata (StataCorp), or Epi Info (Centers of Disease Control and Prevention), among many others.

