### Expected Deliverables

The following will be expected deliverables to be achieved during the project:

Total fungal burden in 406 patients and its changes over time (using quantitative PCR)Fungal microbiome analysis: relative abundance of sputum fungi and their identity (using ITS2 sequencing)Bacterial microbiome analysis: relative abundance of sputum bacteria and their identity (using 16S rRNA gene sequencing)Whole community metagenomics: detailed genomic identification and characterization of abundant members of the sputum microbiome, including gene-level detail Metabolomics profiling of sputum: analysis of host and microbial metabolites in longitudinal sputum samples Integration of culture-dependent and culture-independent data with clinical information to understand disease processes in the patient cohortA genome-scale metabolic model of the diseaseIdentification of fungal and bacteria in the disease to support subsequent epidemiological, treatment, and basic research investigationsTraining and knowledge transfer in cutting-edge microbiome techniques

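### SparCC is named for fungal-bacterial pairs, but it can return them only if the separate 16S and ITS2 tables are pooled, which biases cross-kingdom correlations downward

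*Protocol article*

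**What the plan says.** The Aim 2 section describes 16S sequencing of the DNA extract already used for the fungal work, after which the bacterial results "will be integrated with ITS2 fungal data". On the correlation analysis it states: "For correlations between taxa, a combination of 16S rRNA gene and ITS2 sequencing data from the same samples will be used". Fungal-fungal and bacterial-bacterial pairs are covered by the same sentence as cross-kingdom pairs, and "fungal-bacterial relationships will be interrogated using appropriate software packages, such as SparCC". SparCC is the only correlation tool named, and it is given as an example.

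The Expected Deliverables section confirms that each assay yields a composition: "relative abundance of sputum fungi and their identity (using ITS2 sequencing") for fungi and "relative abundance of sputum bacteria and their identity (using 16S rRNA gene sequencing") for bacteria. The only measure of absolute load is in Aim 1: "Fungal quantitative PCR will be applied to determine the total burden of fungi present in each sample". No bacterial load assay is named.

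**The concern.** SparCC estimates correlations from the variances of log-ratios between components of a single composition. Within such a table the unknown sample total cancels from every ratio. 16S and ITS2 are two assays with two unrelated totals, so a ratio of a fungus to a bacterium does not cancel them: it carries their ratio along. SparCC has no term for this and reads the extra variance as negative correlation.

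Co-abundance patterns are meant to point to potential interactions that Aim 3 then explores. A shift that makes fungi and bacteria look mutually exclusive, and makes members of one kingdom look associated, would put false candidates on that list and could hide true positive fungal-bacterial links.

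**Working it through.** **The plan's own figures.** The article gives no figure for the correlation analysis. Its sample size does reproduce: 1.96² × 0.4 × 0.6 / 0.05² = 368.8, which agrees with "the sample size was determined to be 369 patients" (368.1 with the finite-population correction for 195,013); 369 × 1.10 = 405.9, so 406. That calculation concerns a prevalence, not the network.

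**Why pooling is implied.** Run on the 16S table alone, SparCC returns bacterial pairs; run on the ITS2 table alone, fungal pairs. A fungal-bacterial coefficient exists only if both sets of taxa are columns of one input. Rescaling both kingdoms to absolute load is not available as written, because only fungal load is measured.

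**The bias, algebraically.** Let bacterium *i* and fungus *j* have log-abundance SDs wᵢ and wⱼ and true correlation ρ. In the pooled table

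var(log ratio) = wᵢ² + wⱼ² − 2ρwᵢwⱼ + τ²,

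where τ² is the variance of the log ratio of the two scale factors. For raw counts, a scale factor is read depth over the kingdom's total abundance. Scaling each table to proportions removes read depth but leaves the ratio of the kingdom totals, so τ² shrinks without vanishing.

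Take all taxa independent, with common variance w², B bacterial and F fungal taxa, and D = B + F. SparCC's basic equations (before its exclusion steps) then overstate the bacterial variances by a = τ²F(F−1)/[(D−1)(D−2)] and the fungal ones by b = τ²B(B−1)/[(D−1)(D−2)]. The estimated correlations become:

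- cross-kingdom: (a + b − τ²) / {2√[(w²+a)(w²+b)]}, which is negative
- within bacteria: a/(w²+a); within fungi: b/(w²+b), both positive

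Worked case (assumed): B = 60, F = 30, w = 1, log read-depth SD 1.0 in each assay, counting depth only, so τ² = 1 + 1 = 2. Then a = 2 × 870/7832 = 0.222 and b = 2 × 3540/7832 = 0.904. The cross-kingdom value is (1.126 − 2)/(2 × √(1.222 × 1.904)) = −0.29; within bacteria 0.222/1.222 = +0.18; within fungi 0.904/1.904 = +0.47. Simulation of this setting gave −0.287, +0.185 and +0.483.

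**False-positive rates by simulation.** No true association anywhere; all settings are assumptions.

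Runs with 369 rows, 60 bacterial and 10 to 30 fungal taxa, log read-depth SD 0.2 to 1.0, and a pair flagged if its correlation exceeds 1.96/√369 = 0.102 in absolute value:

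| Input | Mean cross-kingdom correlation | Null cross-kingdom pairs flagged |
|---|---|---|
| Raw counts pooled, SparCC | −0.03 to −0.29 | 14% to 100% |
| Each table scaled to proportions, then pooled, SparCC | −0.01 to −0.04 | 9% to 19% |
| clr within each kingdom, then correlated | 0.00 | 4.7% to 5.3% |

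On raw counts, the mean within-fungal correlation was +0.08 to +0.63.

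Runs with 406 rows, 40 bacterial and 20 fungal taxa, judged against a 5% permutation limit:

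- raw counts, log-depth SD 0.5 for 16S and 1.0 for ITS2: mean about −0.10, 51-56% flagged
- raw counts, both SDs 0.5: 17-19% flagged
- scaled to proportions first, one fungus dominant: 14-60% flagged
- separate clr: 4-6% flagged

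A further set gave 7-58% for pooled counts (mean −0.02 to −0.11), about 8-9% for tables scaled first, and about 5% for separate clr.

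**The case against.** The strongest reply is that the article does not say the tables will be concatenated. It speaks of combining data, offers SparCC only as an example among suitable packages, and cites sources for integration that cannot be checked here. This has weight: the size of the problem depends on processing that is not described. It does not remove the point, because the one tool named cannot deliver the cross-kingdom pairs promised without a joint table, and no other handling is given.

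A second reply is that the deliverables speak of relative abundances, so scaled tables are the likelier input and the largest figures do not apply. That stands in part. Scaling brings the excess down to about 8-19% where no fungus dominates, but not to 5%. Figures above 50% need raw counts with highly variable depth or, in one set of runs, a dominant fungus.

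A third reply is that the network is not the primary outcome. That stands in full. The Abstract makes the diagnostic profile primary, the study is sized on a prevalence, and Aim 2 calls the co-abundance signals potential interactions.

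Two stronger readings are tempting and unsupported. A reader might infer from two sputa per patient, "making a total of 812 samples to be collected", that both specimens enter the network as independent rows. No section says so; the reference to the same samples only pairs the two assays within a specimen. Repeats treated that way would in any case overstate precision, not shift the correlations: the simulated null mean stayed at 0.00. A reader might also infer that false antagonism or mutualism will be reported as a finding. Aim 3 ties those ecological labels to its metabolomic and genome-scale modelling, not to the sign of a SparCC coefficient.

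**Conclusion.** The point holds as a badly chosen method for a stated secondary analysis. SparCC on a joint 16S and ITS2 table biases fungal-bacterial correlations downward and within-kingdom ones upward; the algebra gives the direction and the simulations agree. Every pooled setting tested exceeded the nominal 5%, by little in the mildest case (7%) and by a great deal in the worst.

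The numbers rest on assumed taxa counts, abundance SDs, read-depth variation and flagging rules, none of which the article gives; it states no significance threshold for the network. They show a range, not a prediction. The fungal and bacterial diagnostic profile and the prevalence estimate are not affected. What is at risk is the list of candidate interactions that Aim 2 passes to Aim 3.

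**What to change.** In the Aim 2 section, restrict SparCC to the fungal-fungal and bacterial-bacterial networks, each on its own table. For fungal-bacterial pairs, clr-transform the 16S and ITS2 tables separately, join them, and use a cross-domain method: for example cross-domain SPIEC-EASI, or clr correlation with permutation.

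Keeping SparCC within kingdoms is sensible because plain clr correlation is itself pulled negative when there are few taxa: within fungi the simulated null mean was −0.03 with 30 taxa and −0.11 with 10.

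The cost is a change of analysis wording and another open-source routine. No new data are needed, which matters because the Results section reports enrolment as complete. The downside is that zeros need a pseudo-count, whose value should be stated and varied in a sensitivity analysis. The resulting cross-kingdom associations also describe each taxon relative to the rest of its own kingdom, not its absolute load, and should be reported in those terms.
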